#### Loss to Follow-Up

To investigate whether loss to follow-up differs by arm, we will report this descriptively and use a chi-square test. We will use logistic regression to compare baseline characteristics of participants who completed 4-month follow-up against participants who did not. We will report predictors of loss to follow-up and investigate whether the effect of these differs by arm by testing for an interaction.

#### Assumptions About Missing Data

As we are not aware of similar trials, it is not possible to investigate the pattern of missing data. The complete-case analysis assumes that missing data for participants who did not complete follow-up are similar to data from participants who completed follow-up, conditionally on baseline covariates included in the analysis model (ie, that data are missing at random) [55]. If participants who complete follow-up are more likely to use effective contraception and to find an effective method acceptable compared with those who are lost to follow-up, the observed proportion may overestimate use and acceptability [55].

#### Missing Covariates

The database requires all items on the baseline questionnaire to be submitted in order to proceed to the random allocation. Therefore, there will be no missing baseline covariates.

#### Principal Analyses

##### Descriptive Analysis

We will report a flow diagram of trial participation, as recommended in the Consolidated Standards of Reporting Trials (CONSORT) guidelines [56]. We will report the baseline characteristics by treatment arm. We will also explore the baseline factors associated with retention (see above).

##### Analysis of the Primary Outcome

Both coprimary outcomes are binary, and we will compare the crude proportion who report using effective contraception in each group and the crude proportion who report that at least one method is acceptable in each group. We will estimate the difference between the groups using logistic regression and will report the odds ratio along with the 95% confidence interval and *P* value for evidence against the absence of intervention effect from the model. The primary analysis regression will be adjusted for baseline covariates likely to be associated with the outcome in order to improve the efficiency of the analysis and avoid chance imbalances [57]. The prespecified covariates that we will adjust for are age (16-19 years/20-24 years), number of children (0/≥1), highest education level completed (university/other), and acceptability of effective contraception at baseline (at least one method acceptable/no methods acceptable). Primary outcomes will be analyzed individually, and no formal multiplicity correction will be applied, but interpretation will take into account the multiple tests if only 1 of the 2 outcomes reaches the 5% significance level. We will also report the crude odds ratio between arms.

##### Analysis of the Secondary Outcomes

The analysis of the secondary outcomes will be the similar to the analysis of the primary outcome. We will estimate the difference between the groups using logistic regression, and report odds ratios with 95% confidence intervals and *P* values. All regressions will be adjusted for the prespecified covariates as above (although, with the acceptability of individual methods, the outcome at baseline will replace acceptability of effective contraception).

##### Analysis of the Process Outcomes

The process outcomes perceived norms, personal agency, and intention comprise ordinal scales. We will analyze each scale individually using ordered logistic regression to estimate proportional odds ratios. For knowledge, each correct answer will receive 1 point. The points will be summed and an overall score will be produced. We will use linear regression to test for a difference in mean scores between the arms.

To assess the “dose” of the intervention that the intervention participants received, we will analyze the number of messages that participants reported to have read (all, most, some, none) and whether they stopped the messages. We will report this descriptively.

#### Additional Analyses

##### Sensitivity Analyses

We will conduct sensitivity analyses regarding the missing data. In the first sensitivity analysis, we will consider that data are not missing at random; that participants lost to follow-up did not find at least one method acceptable; and that participants lost to follow-up were not using an effective method of contraception. In the second, we will adjust for the main baseline predictors of missingness. Both sensitivity analyses will be adjusted for the prespecified covariates as above.

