### Intervention

In addition to providing accurate information about contraception (including the dual protection that condoms offer), the intervention messages target beliefs identified in the development phase that influence contraceptive use (eg, specific misconceptions about the side effects and health risks of contraception) and aim to support young women in believing that they can influence their reproductive health. The messages contain the following behavior change methods, adapted for delivery by mobile phone [50]: belief selection, facilitation, anticipated regret, guided practice, verbal persuasion, tailoring, cultural similarity, arguments, shifting perspective, and goal setting. The Tú decides app itself contains standard family planning information and no behavior change methods.

Participants allocated to the intervention group will receive 0 to 3 messages per day (a total of 183 messages) for 120 days. Included in the 183 messages that intervention recipients receive are 7 control messages about the importance of their participation and reminding them to contact the project coordinator if they change their number.

The message sets start with 6 days of messages with general information about the study, such as information about what they will receive over the next 120 days, how to stop the messages, who to contact if they change their number, how to keep the messages private, and information about who to call if they feel unsafe as a result of someone reading the messages.

On days 119 and 120, the intervention includes 4 messages: 1 that indicates that the messages have ended, 1 that provides a link to the database to complete the follow-up questionnaire, 1 that gives reassurance that the information they provide is confidential, and a final message stating that their participation is helping to determine the best ways to provide reproductive health services in Bolivia.

Details regarding the development and a description of the intervention will be reported in a forthcoming publication.

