### Control

Participants allocated to the control group will have access to the same Tú decides app pages as the intervention group. Control participants will also receive 16 messages about trial participation over 120 days. The first 4 days include 6 messages that introduce the study, as well as providing information about what they will receive over the next 120 days, how to stop the messages, and who to contact if they change their number. They then receive 2 messages a month for 3 months: 1 about the importance of their participation and 1 reminding them to contact the project coordinator if they change their number. On day 105, they will receive 1 message about the importance of their participation. On day 120, participants will receive 3 messages: 1 that provides information on how to complete the follow-up questionnaire, 1 that gives reassurance that the information they provide is confidential, and a final message stating that their participation is helping to determine the best ways to provide reproductive health services in Bolivia.

All participants will receive usual care and will be free to seek any other support, whether existing or new.

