### Analyses

#### General Statistical Considerations

The analysis of the data will follow the plan specified below. There will be no interim analyses and therefore no stopping rules. We will analyze participant data according to the arm that they were allocated to and will include only participants with complete outcome data in the primary analysis (a complete-case analysis). All statistical tests will be 2-sided. We will report all effect estimates with a 95% confidence interval and associated *P* value. Statistical significance will be considered at the 5% level, but interpreted with caution considering the 2 primary outcomes. We will use the latest version of Stata (StataCorp LLC) for analyses.

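### No planned analysis lets lost participants differ from followed ones by arm: the only not-missing-at-random scenario sets every lost woman in both arms to failure

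*Protocol article*

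**What the plan says.** Under General Statistical Considerations, the protocol article restricts the primary analysis to participants with complete outcome data. Assumptions About Missing Data states that this rests on missing at random given the model covariates. It warns that, if completers are more likely to use a method and to find one acceptable, "the observed proportion may overestimate use and acceptability". That warning concerns the level in the observed data, not the comparison between arms.

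Sensitivity Analyses then names two analyses. The first is labelled not missing at random. For the use outcome it supposes that "participants lost to follow-up were not using an effective method of contraception". Its counterpart for the acceptability outcome reads "participants lost to follow-up did not find at least one method acceptable". Neither assumption distinguishes the arms. The other analysis is described thus: "In the second, we will adjust for the main baseline predictors of missingness". Both keep the prespecified covariates.

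Loss to Follow-Up says: "To investigate whether loss to follow-up differs by arm, we will report this descriptively and use a chi-square test". It also plans to model predictors of loss and to test whether they act differently by arm. No sensitivity analysis is tied to what those checks show.

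**The concern.** A between-arm comparison is biased by missing data when the lost differ from the followed to a different degree in each arm. Neither planned analysis varies that. The first gives the lost the same value in both arms. The second conditions on more baseline variables but stays within missing at random.

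Arm-specific departure is conceivable here. Participants learn their allocation soon after messages start, receive 183 or 16 messages on a sensitive subject, can stop the messages and can withdraw from follow-up. With 20% loss planned, readers will want to know how far the lost would have to differ by arm before the conclusion changes. The planned scenario cannot tell them. If retention is unequal, it also moves the contrast for a reason unrelated to treatment, unless all lost women really are failures.

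**Working it through.** **Inputs.** From Sample Size: 44% versus 54% use, odds ratio 1.49, 90% power, 1048 evaluable, 20% loss, 1310 randomised. From Study Design: 1:1 allocation, so 655 per arm. From General Statistical Considerations: two-sided 5% tests. The split of loss between arms is not in the document; every unequal split below is an assumption averaging 20%.

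**The plan's own figure.** A two-proportion test with pooled variance and no continuity correction needs 524 per arm, 1048 in total (power 90.05%). Then 1048 / 0.80 = 1310, and (0.54/0.46) / (0.44/0.56) = 1.49. The sample size reproduces and is not in question.

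**What missing = failure does.** If p is the success rate among those followed and l the loss, the analysed rate is p × (1 − l). The analysed difference is then exactly

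(p_I − p_C) × (1 − mean loss) + mean p × (l_C − l_I).

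The first term shrinks the observed effect. The second adds the retention difference, scaled by the success rate.

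- *Equal loss, 20%/20%, 54% v 44%:* 0.432 − 0.352 = 8.0 points, odds ratio 1.40, power about 84%. With no effect, the difference is 0 and rejection stays at 5%.
- *No effect (44% in both), loss 15% intervention, 25% control:* 0.44 × 0.85 = 0.374; 0.44 × 0.75 = 0.330; difference 4.4 points, odds ratio 1.21. Null SE = √(0.352 × 0.648 × 2/655) = 0.0264, so the expected z is about 1.67. Rejection is 38.5% (38.6% in favour of the intervention in 100,000 simulated trials).
- *No effect, loss 17.5%/22.5%:* 36.3% v 34.1%, odds ratio 1.10; rejection in favour of the intervention 13.0% against a nominal 2.5%.
- *54% v 44%, loss 25%/15%:* 0.10 × 0.80 − 0.49 × 0.10 = 3.1 points (40.5% v 37.4%), odds ratio 1.14, power 21%.
- *54% v 44%, no difference left:* 0.08 / 0.49 = a 16.3-point loss gap, about 28.2% v 11.8%.

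In all these cases lost women are taken to resemble those followed in their own arm. The complete-case test then keeps 5% error and about 90% power.

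**What stays untested.** Take equal 20% loss and 54% v 44% among those followed, and let the lost have rates m_I and m_C. The all-randomised difference is 0.80 × 0.10 + 0.20 × (m_I − m_C).

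| Lost, intervention | Lost, control | Difference (points) | Odds ratio |
|---|---|---|---|
| 0% | 0% (planned scenario) | 8.0 | 1.40 |
| 20% | 20% | 8.0 | 1.39 |
| 0% | 20% | 4.0 | 1.18 |
| 20% | 44% | 3.2 | 1.14 |
| 0% | 44% | −0.8 | 0.97 |

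Under equal loss, any common rate for the lost gives 8.0 points. Only rows where the arms differ test the contrast. The point estimate reaches zero when m_I − m_C = −0.08 / 0.20 = −40 points.

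**The case against.** The strongest reply is that the 38% comes from judging the scenario in a world it was built to leave. It supposes that lost women resemble those followed, which is where the complete-case analysis is valid. If lost women truly are failures, missing = failure is the correct analysis. This stands. A reader might infer that the trial has a 38% false-positive rate. The document does not support that: the significance level governs the primary analysis, no decision rule hangs on the sensitivity analysis, and a divergence between the two would be visible.

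A reader might also infer that missing = failure is simply wrong. For use it is not: Eligibility Criteria admit only women not using effective contraception, so the scenario carries entry status forward. It is also the extreme form of the worry in Assumptions About Missing Data. For acceptability the defence is weaker, since acceptability is measured at baseline and the scenario overrides a positive answer. The size of that cannot be given, because the article reports no baseline rate.

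Nor is this the trial's only check on informative loss. The chi-square test of loss by arm would detect 15% v 25% with 99.5% power, but 17.5% v 22.5% with only about 62%. Such checks describe loss; they do not show what it does to the effect.

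Evidence that loss will differ by arm is thin. Staff are not told allocation, nonresponders are contacted up to three times without distinction by arm, and engagement messages go to both arms. The closing prompts are described differently, "1 that provides a link to the database to complete the follow-up questionnaire" for intervention and "1 that provides information on how to complete the follow-up questionnaire" for control, but this may be only summary wording, and online entry is open to everyone. Nothing here rests on it. Nor is it a fault that a fixed scenario carries no imputation uncertainty, since it has none to carry.

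Finally, tipping-point detail often sits in a statistical analysis plan, which is not shown. But the article says the analysis will follow the plan it sets out, and it names these two analyses. The point is about that stated choice.

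**Conclusion.** The point holds as a cheap improvement, not as an error in the primary analysis. Of the two stated missing-data analyses, one applies a single value to the lost in both arms and the other still assumes missing at random. The effect estimates are therefore never tested against departures that differ by arm.

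Under equal 20% loss, the planned scenario can only turn 10 points into 8. Under unequal loss it shifts the contrast by the success rate times the retention gap: 4.4 points for an assumed 10-point gap at 44%, with about 38% rejection in that sensitivity analysis alone. These sizes rest on assumed loss splits and on lost women resembling those followed.

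The untested departures should not be exaggerated either. At the planned effect and equal 20% loss, the point estimate reaches zero only if lost intervention women are 40 points below lost control women, although smaller gaps weaken it materially (3.2 to 4.0 points in the table). A reported tipping point would let readers judge this for the observed data.

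**What to change.** Keep missing = failure as one labelled scenario, noting that for use it equals entry status and for acceptability it overrides baseline answers. Report it beside loss by arm.

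Add, for both coprimary outcomes, a delta-adjusted (pattern-mixture) analysis by multiple imputation:

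- Impute from arm, the four prespecified covariates (which include baseline acceptability) and the baseline predictors of missingness.
- Multiply the odds of success in missing relative to observed participants by a factor running from 1 towards 0, set separately in each arm, and include the case where the missing are worse in the intervention arm only.
- Fit the primary adjusted logistic model to each imputed set, combine the results, and report the grid and the tipping point at which the conclusion changes.

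Fix the grid before the analysis by arm. If the full analysis plan already contains such an analysis, no change is needed beyond saying so. The cost is a paragraph of text and some extra programming and reporting; no new data are required.

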##### Subgroup Analysis

Recognizing that the trial is not powered to detect effect differences in subgroups, we will conduct exploratory subgroup analyses for the coprimary outcomes to determine whether the intervention effect varies by baseline characteristics. The prespecified subgroups are age (split at the median); marital status (married/not married); number of children (0/≥1); geographic location (El Alto/La Paz); occupation (in education/other); and highest education level completed (university/other). Within the prespecified subgroups, we will assess heterogeneity of treatment effect with a test for interaction [58-62]. Interaction test *P* values will be presented but will be interpreted with caution, due to the exploratory nature, the multiple tests performed, and the low power of the interaction test. We will estimate odds ratios along with 95% CIs for each subgroup without *P* values. As this is an exploratory analysis of potentially influential characteristics that are not justified a priori, we will not hypothesize effect directions.

##### Contamination

To assess the potential for contamination, we will report the proportion of control group participants who read another participant’s messages and the proportion of intervention participants whose messages were read by another participant.

##### Analysis of Pooled Trial Data

We are conducting trials of a similar intervention in 2 other countries. If the results of the other trials are available, we will conduct the principal analyses on the pooled dataset.

The datasets used and analyzed during this study are available from the corresponding author on reasonable request.

### Participants’ Rights and Safety

Participants will have the right to withdraw at any time during their involvement, without having to give a reason. Participants can withdraw by contacting the project coordinator. Acting on a participant’s request to withdraw from the trial, we will change the participant’s status to “withdrawn” and exclude the person from the list of participants who are due for follow-up. Participants’ participation and personal identifiable data will remain confidential and research data will be anonymized.

In the formative work, we explored young people’s views on confidentiality about receiving messages on their mobile phone. While the majority of participants did not report concerns regarding receiving messages about contraception on their mobile phone, it is possible that some participants will want to keep the messages confidential from certain people (eg, partner, parents) and that these people might view the messages. The messages remind participants that they can delete the messages and provide instructions on how to keep the messages private. We will provide participants with information on support services that they can contact if they feel unsafe as a consequence of the messages being read. We will review physical violence during participants’ involvement in the trial reported on the follow-up questionnaire.

## Results

Recruitment commenced on March 1, 2017 and was completed on July 29, 2017. The estimated completion date for the final participant recruited (final data collection date for the primary outcome) is January 2018.

## Discussion

Among young women in La Paz and El Alto with an unmet need, the results of this trial will provide evidence for the effect of the intervention on their use of and attitudes toward effective contraception. The analysis of the secondary and process outcomes may provide evidence for the effect of the intervention on attitudes toward the individual effective methods, service use, unintended pregnancy, induced abortion, and the psychological processes that may have been altered by the intervention.

Because this trial is being conducted among young women with an unmet need for contraception in a context where information about contraception is low, it is reasonable to assume that enrolling in the trial will be popular. While this is an advantage with regard to meeting the recruitment target, it is possible that participants will tell their friends about the trial and that they will also enroll. While this is desired in a nontrial context, this could lead to contamination if the intervention messages are shared with control participants during the trial. To minimize this, participants will not be recruited through schools.

Because the intervention is being delivered through the Tú decides app, participants must own a personal Android mobile phone to take part in the trial. Although the intervention development work indicated that the majority of young people in Bolivia own a personal Android mobile phone, not everyone in the target group will. It may be that young people less likely to use and to find contraceptive methods acceptable are more likely to not own an Android phone, which would limit the generalizability of the findings. Smartphone ownership continues to increase rapidly, however, so it is likely that a greater proportion of young people from different socioeconomic communities will be able to receive the intervention in the future.

The trial will assess the effect of sending instant messages containing behavior change methods in addition to the app; it is not assessing the effect of the app itself. It is possible that the app, which provides standard family planning information, could have an effect on effective contraceptive use and acceptability of effective contraception. If the app itself is very effective, the added benefit of the instant messages will be lower. The results of the study will add to current research on mobile phones for intervention delivery and will determine whether mobile phones can be an important adjunct to sexual and reproductive health service provision in Bolivia.

## Appendix

Multimedia Appendix 1 Trial information sheet.

Multimedia Appendix 2 Trial consent form.

Multimedia Appendix 3 Baseline questionnaire.

Multimedia Appendix 4 Follow-up questionnaire.

